### Recruitment

The recruited subjects will be patients who provide a written consent of their own free will to participate after being fully informed of and fully understanding the study. At Kansai Medical University Hospital, between 10 and 15 patients undergo hepatectomy per month. Upon admission to Kansai Medical University Hospital, study participants will be recruited by surgeons participating in the study. The surgeon will obtain informed consent from the participant. Study subjects will receive no financial incentives for participation.

### Inclusion criteria

Male or female aged 20 or older at the time of consentPatients with hepatobiliary disease and will be undergoing hepatectomyLaparotomic or laparoscopic hepatectomyAny extent of liver resectionAny hepatobiliary disease (including hepatocellular carcinoma, intrahepatic cholangiocarcinoma, and metastatic liver cancer)3.Patients who provide a written consent of their own free will to participate after being fully informed of and fully understanding the study

### Exclusion criteria

Patients who meet any of the following criteria will not be enrolled in this study:
Patients with severe liver dysfunction or severe kidney dysfunction (patients satisfying any of the following: total serum bilirubin > 3.6 mg/dL, AST > 175 U/L, ALT > 175 U/L, creatinine > 3 mg/dL, or eGFR < 30 mL/min/1.73m^2^)Poorly controlled diabetesFemale patients who are or might become pregnantFemale patients who are lactatingPatients who received another test drug or investigational drug within 3 months of consentPatients who might undergo resection of an organ besides the liver (including the stomach, colon, and lung but excluding the gall bladder) at the time of hepatectomyPatients who will require biliary tract reconstruction at the time of hepatectomyPatients who will undergo emergency surgery (including for ruptured liver tumor)Patients whom the principal investigator determined to be unsuitable for the study

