### Randomization and allocation concealment

After the research team obtains patient consent from the recruited participants, web-based registration and minimization method of random allocation will be performed at the data center of Medical Research Support, a company located in Japan that is independent of the research team. Medical Research Support will generate web-based randomization sequences. The research team cannot access the randomization process and will be informed of the results of the randomization via email from Medical Research Support. The minimization method of random allocation prevents the prediction of study allocation. Then, the registration numbers and the allocation results will be added to the eligibility criteria checklist. The information will be faxed to the data center, resulting in patient registration.

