### Blinding

In this double-blind trial, the device that supplies air is manufactured so that it is indistinguishable by appearance from the hydrogen gas generator. The markers are pasted on the behind of generators to distinguish which generator is the hydrogen gas generator or the air generator. Only the principal investigator knows the meaning of marking, whereas the research stuff are not informed of the meaning of marking. The web-based patient allocation was known only to the person responsible for statistical analysis, the person in charge of support for the research and development program, and the principal investigator. However, research staff and patients cannot know the allocation. If unblinding is deemed to be necessary, such as for treatment of emergencies, the principal investigator should open the allocation. Unblinding is not necessarily a reason for discontinuation of study gas.

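### The principal investigator holds both an open-ended veto on entry and the past allocations, and the claim that minimisation prevents prediction is untrue for that person, so entry is exposed to selection bias.

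*Protocol article*

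**What the plan says.** Four statements in the protocol article bear on this point.

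- **Exclusion criteria**, last item: "Patients whom the principal investigator determined to be unsuitable for the study". This is a judgement without criteria, given to one named role.
- **Blinding**: "The web-based patient allocation was known only to the person responsible for statistical analysis" and to two further people, of whom the principal investigator is one. The same section adds, on the generators: "Only the principal investigator knows the meaning of marking". Other research staff and patients are said to be kept unaware.
- **Randomization and allocation concealment**, on predictability: "The minimization method of random allocation prevents the prediction of study allocation".
- **Randomization and allocation concealment**, on process: "web-based registration and minimization method of random allocation will be performed at the data center of Medical Research Support". This firm is separate from the investigators. On access and reporting: "The research team cannot access the randomization process and will be informed of the results of the randomization via email from Medical Research Support". On the paperwork: "Then, the registration numbers and the allocation results will be added to the eligibility criteria checklist". A fax to the data centre afterwards completes registration.

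Under Recruitment, participating surgeons approach patients and obtain consent. The trial has one site and 68 patients.

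**The concern.** Allocation concealment means that whoever decides on entry cannot foresee the arm. Here one person can refuse a patient for an unspecified reason and also knows how earlier patients were allocated. The article's reassurance is that minimisation prevents prediction. But minimisation favours an arm according to past allocations and the new patient's factor levels, so for a holder of past allocations it is more predictable than simple randomisation.

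If frailer patients were turned away more often when hydrogen was favoured, even without intent, the hydrogen group would start with better prognosis. Its day-3 QoR40 would then be higher without any treatment effect. The stated primary analysis is an unpaired t-test with no baseline adjustment described.

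**Working it through.** **Scale of the trial.** The Sample size estimation section gives means of 151 and 137 (difference 14), a spread of 30, two-sided alpha 0.20 and power 70%. The formula is n per group = 2(z₀.₉₀ + z₀.₇₀)²(30/14)² = 2 × (1.282 + 0.524)² × 4.59 ≈ 30. The t-based version gives 30.3, so 31, as stated. The figure reproduces only if 30 is read as a standard deviation, although the text calls it a variance. I use SD 30 below.

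**Can a holder of past allocations predict the next arm?** I simulated two-arm minimisation with n = 68 and balanced binary factors. The guesser knows past allocations and factor levels and names the favoured arm; ties score 0.5. The number of factors and the assignment probability p are assumptions, because the article gives neither. Share guessed correctly:

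| Factors | p = 1 | p = 0.8 | p = 0.7 |
|---|---|---|---|
| 1 | 75% | 69% | 64% |
| 2 | 86% | 73% | 67% |
| 3 | 89% | 75% | 68% |
| 4 | 92% | 76% | 68% |

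Simple randomisation gives 50%. A random element lowers predictability, but no setting examined brings it to 50%. Someone without past allocations stays near 50%.

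**What could selection do?** Take an extreme rule: the poorest-prognosis fifth is always refused when hydrogen is favoured.

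1. Cutting the lowest fifth from a normal variable raises its mean by φ(z₀.₂)/0.80 = 0.28/0.80 = 0.35 SD.
2. Let g be the correct-guess rate. The difference between arms in the share of patients who entered when hydrogen was favoured is 2g − 1. For g = 0.73 this is 0.46; for g = 0.89 it is 0.78.
3. With correlation ρ between the prognosis that the investigator can see and day-3 QoR40, the bias is ρ × 30 × 0.35 × (2g − 1).
4. At ρ = 1: 30 × 0.35 × 0.46 = 4.8 and 30 × 0.35 × 0.78 = 8.2 points.
5. At ρ = 0.3 to 0.5 (assumed): 0.3 × 4.8 = 1.4 up to 0.5 × 8.2 = 4.1 points.

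Simulations of this rule agree closely: about 5 to 8 points at ρ = 1, and an outer range of 1.4 to 4.5 points at ρ = 0.3 to 0.5.

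**Against the test.** With 31 per group the standard error is 30 × √(2/31) = 7.6 points. A shift of 4.1 points is 4.1/7.6 = 0.54 standard errors. By normal approximation, the two-sided 5% test would then reject under no effect with probability 1 − Φ(1.96 − 0.54) + Φ(−1.96 − 0.54) ≈ 8%.

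**Does the described process close the route?** The independent data centre and the team's lack of access to the randomisation process protect against people who do not know past allocations. They do not take that knowledge from the principal investigator. The article does not say that suitability is settled before allocation is requested. It has the allocation written on the eligibility checklist before the fax that completes registration. It also has results emailed to the research team, which conflicts with the Blinding section.

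**The case against.** A discretionary exclusion is routine and is not an error in itself. The fault is that it is assigned to someone who holds the allocations. Surgeons recruit and obtain consent, so the principal investigator's route is a veto. For surgeons without the list, the sentence on prediction does little harm. No passage says that the principal investigator reviews each patient's minimisation factors or keeps running totals; that this is possible at a single site is a fair inference, not a stated fact. The Blinding section also has the principal investigator open the allocation when unblinding is needed, which sits awkwardly with already knowing it. All of this stands and limits the point, but does not remove it: the text still puts the veto and the allocations in the same hands.

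A reader might go further in four ways that the document does not support.

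- **That selection has occurred.** Nothing shows this.
- **That the bias would be 5 to 8 points.** That needs prognosis to correlate perfectly with day-3 QoR40, as if the score could be seen before surgery.
- **That no analysis could detect or remove it.** QoR40, liver function, dietary intake and steps are measured preoperatively. Imbalance could show there, and adjustment for preoperative QoR40 would remove part of it, though not selection on unrecorded frailty.
- **That the missing factors or random element are a fault.** An article may leave these to the full protocol. The 86% to 89% figures (two or three factors) assume deterministic minimisation, which the article does not state.

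**Conclusion.** The point holds as an exposure to selection bias at entry, created by the Exclusion criteria and Blinding sections together. The sentence that minimisation prevents prediction is wrong for anyone with the past allocations, with or without a random element. Under two or three assumed binary factors and p of 0.8 to 1, that person guesses about 73% to 89% of arms.

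Under the extreme refusal rule, the spurious difference is about 1.4 to 4.5 points at a correlation of 0.3 to 0.5, or roughly 10% to 32% of the planned 14 (1.4/14 and 4.5/14). Refusing only some of these patients would give less. These sizes rest on assumed factors, assignment probability, correlation and refusal rule. The conflict of roles and the incorrect sentence rest on the text alone. The change should be made because it costs very little.

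**What to change.** 1. Have eligibility, including the unsuitable judgement, decided by an existing subinvestigator with no access to allocations or the marker key. That person signs, records the reason on the screening log, and locks the decision before allocation is requested. Alternatively, move the allocation list and marker key from the principal investigator to an independent holder such as the data centre; the Blinding section's unblinding step would then need matching wording.
2. Delete the sentence that minimisation prevents prediction. Adding a random element would not replace step 1, since predictability stays near 75% at p = 0.8.
3. Reconcile the emailing of results to the research team, and their entry on the eligibility checklist, with the statement that research staff do not know the allocation. Step 1 depends on this: a subinvestigator who receives those emails is not without access.

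The cost is a wording amendment and a change of signatory among existing staff, with no effect on sample size. Enrolment began on 9 March 2021, so the change protects only patients still to be enrolled. For those already screened, reporting the number and reasons of exclusions under this item would let readers judge the exposure.

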### Randomization and allocation concealment

After the research team obtains patient consent from the recruited participants, web-based registration and minimization method of random allocation will be performed at the data center of Medical Research Support, a company located in Japan that is independent of the research team. Medical Research Support will generate web-based randomization sequences. The research team cannot access the randomization process and will be informed of the results of the randomization via email from Medical Research Support. The minimization method of random allocation prevents the prediction of study allocation. Then, the registration numbers and the allocation results will be added to the eligibility criteria checklist. The information will be faxed to the data center, resulting in patient registration.

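### The protocol contradicts itself on whether research staff learn the allocation, and it unblinds the principal investigator and the responsible statistician by design

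*Protocol article*

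**What the plan says.** Randomization and allocation concealment (Protocol article) describes web registration and minimization at an independent data centre after consent. The research team has no access to the process but "will be informed of the results of the randomization via email from Medical Research Support". Next, "the registration numbers and the allocation results will be added to the eligibility criteria checklist", and the information is faxed to the data centre, which is said to result in registration. The section also asserts: "The minimization method of random allocation prevents the prediction of study allocation".

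The Blinding section calls the trial double-blind and says that "the device that supplies air is manufactured so that it is indistinguishable by appearance from the hydrogen gas generator". Markers on the back tell the two kinds of generator apart. "Only the principal investigator knows the meaning of marking". The allocation is "known only to the person responsible for statistical analysis, the person in charge of support for the research and development program", and to the principal investigator. It then states that "research staff and patients cannot know the allocation". The principal investigator also opens the allocation if unblinding is needed.

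Two other places bear on this. The last exclusion criterion reads "Patients whom the principal investigator determined to be unsuitable for the study". Statistical analysis and Analysis of efficacy make the per-protocol population the primary one, with an intention-to-treat analysis alongside.

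**The concern.** One section sends the allocation result to the research team and puts it on a site form. The next says that research staff cannot know it. If the first is followed, staff who recruit, treat or assess patients may know the arm.

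This matters because the outcomes leave room for influence. The primary endpoint is a self-completed recovery score. Pain is recorded by nurses or physicians after interview, and complications are graded by the attending physician. The role that decides discretionary exclusions holds the full allocation list. The role responsible for the analysis knows the arms while the primary comparison depends on who counts as per-protocol. Three things are at stake: concealment of the next assignment, even-handed care and assessment, and neutral construction of the analysis set.

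**Working it through.** No arithmetic applies. The check sets the statements side by side.

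**1. Do research staff know the allocation?**

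| Section | Statement |
|---|---|
| Randomization and allocation concealment | The research team is told the result by email, and the result goes on the eligibility checklist |
| Blinding | Three roles know the allocation; research staff cannot |

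The first section does not limit the email to the three roles and does not say that only a device code is sent. The same sentence group has the research team obtaining consent, and Recruitment says that the surgeons obtain it. Read in its ordinary sense, the research team therefore includes the recruiting surgeons and is wider than the three code holders. A second exposure is the checklist, a site document that carries the allocation. The two sections cannot both be followed as written.

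**2. Who is unblinded by design?** The Blinding section names the responsible statistician, a development-program support person and the principal investigator. This is stated openly and needs no inference.

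- *Principal investigator.* This role knows the allocations and the device marking, and holds the discretionary exclusion.
- *Statistician.* Membership of the primary set requires the minimum inhalation on at least 2 days and a measured day-3 score. The stated daily duration of 3 h over 2 days gives 3 × 2 = 6 h, and the text adds a range of at least 6 h to less than 7 h without saying how that range is to be applied. Interventions and data collection adds that patients who stop the gas early have no further QoR40 assessment. Some membership decisions may therefore remain, and they would be made with the arms known.

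**3. Does minimization prevent prediction?** Minimization assigns the next patient in light of the earlier patients' characteristics and allocations. Someone who knows all earlier allocations is better placed to anticipate the next one than someone who knows none. How much better depends on the balancing factors and on any random element, and the article gives neither. The flat claim is too strong, but the degree of predictability cannot be calculated.

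**4. Does registration come before or after allocation?** The section first names web registration together with minimization. It ends by saying that registration results from the fax, which by then carries the allocation. Under the first reading every allocated patient is already registered. Under the second, a patient could be allocated, the arm seen, and the form not sent, so the randomized set could be incomplete. The text supports neither reading consistently.

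**5. How many patients are affected?** The email and checklist steps apply to every enrolment. If that section governs, they concern all 68 patients. If the Blinding section governs, they concern none as far as research staff are concerned. The article does not say which governs.

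**The case against.** The strongest reply is that the two sections can be read together. The email may go only to the three named roles, or may carry only a device marker whose meaning staff do not know. A condensed article may leave such detail to the full protocol. The fax may be paper confirmation of a web registration already complete, since registration numbers exist when the checklist is filled in. The per-protocol set rests largely on recorded criteria, with inhalation time logged per 24 h, and an intention-to-treat analysis is also planned.

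Part of this stands. The sequence is unclear rather than proven wrong, and the statistician's room for discretion is limited. But the benign reading of the email has to be supplied from outside the text. Two current statements conflict, which differs from an omitted detail.

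Stronger readings are tempting, and the document does not support them:

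- *That the trial as a whole is not double-blind.* Nothing shows that patients learn their arm. The devices look alike, and patients complete the primary endpoint themselves.
- *That one emergency code-break would reveal every patient.* This needs marks shared across generators and their meaning disclosed to staff. The Blinding section says neither.
- *That ward staff run the face-to-face adherence sessions.* Methods/design does not say who does. Nor does any section say that attending nurses receive the email or see the checklist.
- *That the bias amounts to a given number of points.* Any such figure would have to be assumed, because the document offers no basis for one.

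**Conclusion.** The point holds in this form. The protocol contradicts itself on whether research staff know the allocation. The principal investigator and the responsible statistician are unblinded by design, so the double-blind label does not extend to them. The statement about minimization claims too much, and the order of registration and allocation is inconsistent.

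The size is one of scope: the affected steps apply to each of the 68 planned enrolments, and the effect on the QoR40 comparison cannot be quantified from the document. The conclusion assumes that the research team has its ordinary meaning, including the staff who obtain consent. If the email in practice reaches only the named roles or carries only a code, the first element reduces to a correction of text. The unblinded investigator and statistician remain either way. Because the primary endpoint is subjective and the remedy is cheap, the matter should be settled in the protocol.

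**What to change.** 1. Reconcile Randomization and allocation concealment with Blinding: state who receives the email and what it contains.
2. Complete the eligibility check and registration before minimization is run, and describe the fax accordingly.
3. Send site staff only a registration number and a coded device identifier, and keep the arm off the eligibility checklist.
4. Have the existing independent data centre hold the allocation code, instead of the person who decides eligibility. The unblinding procedure in the Blinding section must be reconciled with this.
5. Keep the responsible statistician blinded until the analysis sets and the data are locked.
6. Delete the claim that minimization by itself prevents prediction.
7. State exactly which roles are blinded and which are not.

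The cost is a revised email and checklist template, a coded identifier for the devices, and a code-holding procedure at a data centre already engaged. The downside is a possible short delay when a code has to be obtained through the data centre. If current practice already works this way, only the text needs correcting.

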### Blinding

In this double-blind trial, the device that supplies air is manufactured so that it is indistinguishable by appearance from the hydrogen gas generator. The markers are pasted on the behind of generators to distinguish which generator is the hydrogen gas generator or the air generator. Only the principal investigator knows the meaning of marking, whereas the research stuff are not informed of the meaning of marking. The web-based patient allocation was known only to the person responsible for statistical analysis, the person in charge of support for the research and development program, and the principal investigator. However, research staff and patients cannot know the allocation. If unblinding is deemed to be necessary, such as for treatment of emergencies, the principal investigator should open the allocation. Unblinding is not necessarily a reason for discontinuation of study gas.

